## APPENDIX 4: Study Web Page Example

The screenshot below shows an example of a study page in the USC Clinical Studies Directory. The study web pages used in this research project will use the same type of template but will differ in that they will have a disease specific parent page that lists all recruiting trials enrolled in this study – one parent page for each selected cancer type: lung cancer, colon cancer, breast cancer, prostate cancer, kidney cancer and lymphoma. For example, all recruiting lung cancer studies enrolled in this study will be listed on this parent page and have individual pages as shown below.

The easy-to-use contact form asks for the name and email of a user and triggers an email to the SC CTSI team ([name] and [name]) who will triage the request to the correct disease contact at USC Norris. The web page content used for this research will be submitted to the IRB once we enroll the trials and know their focus and consent information. The consent information will guide the content we use on the web pages.

### **Example of a clinical study web page in the USC Clinical Studies Directory**

**Kecik Medicine of USC**

Improving dermatologic care for psoriasis patients

## Purpose

We seek to evaluate an online psoriasis care delivery model. Through this online model, patients can see the dermatologist online rather than coming into the office for a visit. The model is designed to increase patient and primary care physician access to dermatologists. We want to find out if this online model ultimately improves patients' severity and quality of life.

**Keywords:** psoriasis, dermatology, access, telehealth, telemedicine, skin disease

## What's involved?

|                                                                      |                                                                                                                                |                                      |
|----------------------------------------------------------------------|--------------------------------------------------------------------------------------------------------------------------------|--------------------------------------|
| TRIAL LENGTH
1 year                                        | NUMBER OF VISITS
<1hr per week                                                                                       | PRESCRIPTION
None          |
| PROCEDURES
Quarterly surveys that can be completed at home | CASH PAYMENT
\$100 for baseline visit and \$50 for completion of quarterly questionnaires for a total of up to \$300 | MEDICAL COST COVERAGE
None |

## Why participate?

85% of clinical trials face delays due to lack of participation. Be a part of the solution!

[#Join](#)

## Eligibility

### Must have

- ✓ 18 years and older
- ✓ Diagnosed psoriasis
- ✓ Access to the internet and to a digital camera or phone with camera features
- ✓ Reside in California

### Can't have

There are no exclusion criteria

## We respect your privacy!

All the information you give us is stored in a secure, password protected database. All the information that you choose to share will be kept private and confidential. Read University of Southern California's Privacy Policy here.

Powered by SC ITUs

**Kecik Medicine of USC**

Advanced technology. Innovative medicine and compassionate care.  
[USC logo] | Learn more

[Learn More About Us](#)
[Locations](#)
[About Kecik Medicine](#)
[Contact Us](#)

## APPENDIX 5. DATA DICTIONARY WITH ALL MEASURES OF SUCCESS USED IN THIS RESEARCH PROJECT

| Measurement       | Variable name        | Type of variable | Variable label                                                  | Value labels                                                                                                                           | Comments   |
|-------------------|----------------------|------------------|-----------------------------------------------------------------|----------------------------------------------------------------------------------------------------------------------------------------|------------|
| Surveillance data | sm_topic             | Text             | Disease topic                                                   | 1=non-small cell lung cancer
2=colon cancer 3=breast cancer 4=prostate cancer
5=kidney cancer 6=lymphoma                         |            |
| Surveillance data | user_name            | Text             | User Twitter name                                               |                                                                                                                                        |            |
| Surveillance data | user_description     | Text             | User Twitter description                                        |                                                                                                                                        |            |
| Surveillance data | user_location        | Text             | User Twitter location                                           |                                                                                                                                        |            |
| Surveillance data | twitter_message      | Text             | Twitter message that mentions any of the targeted disease terms |                                                                                                                                        |            |
| Surveillance data | tate_sent            | Numeric          | Date of Twitter user message                                    |                                                                                                                                        | mm/dd/yyyy |
| Contact data      | contact_message      | Text             | Content of contact message                                      |                                                                                                                                        |            |
| Contact data      | date_sent            | Numeric          | Date of contact message                                         |                                                                                                                                        | mm/dd/yyyy |
| Contact data      | sol_acknowledgement  | Numeric          | Contact acknowledged solicitation                               | 1=yes 0=no                                                                                                                             |            |
| Contact data      | date_acknowledgement | Numeric          | Date contact acknowledged solicitation                          |                                                                                                                                        | mm/dd/yyyy |
| Contact data      | patient              | Numeric          | Is the contacted person a cancer patient?                       | 1=yes 0=no                                                                                                                             |            |
| Contact data      | patient_cancer_type  | Text             | Type of cancer contact was diagnosed with                       | 1=non-small cell lung cancer
2=colon cancer 3=breast cancer 4=prostate cancer
5=kidney cancer 6=lymphoma
7=Other              |            |
| Contact data      | eligibility          | Numeric          | Is the contacted person eligible for one of the trials?         | 1=yes 0=no                                                                                                                             |            |
| Contact data      | first_name           | Text             | Contact's first name                                            |                                                                                                                                        |            |
| Contact data      | last_name            | Text             | Contact's last name                                             |                                                                                                                                        |            |
| Contact data      | gender               | Numeric          | Gender                                                          | 1=Male 2=Female                                                                                                                        |            |
| Contact data      | race/ethnicity       | Numeric          | Race/ethnicity                                                  | 1=African American / Black
2=American Indian / Alaska Native 3=Asian / Pacific Islander 4=Hispanic 5=Middle Eastern 6=White 7=Other |            |

|              |                       |         |                                                                                                                                                                              |                                                                                                                                                                                                                                                                                                                                                                     |                                                                                                |
|--------------|-----------------------|---------|------------------------------------------------------------------------------------------------------------------------------------------------------------------------------|---------------------------------------------------------------------------------------------------------------------------------------------------------------------------------------------------------------------------------------------------------------------------------------------------------------------------------------------------------------------|------------------------------------------------------------------------------------------------|
| Contact data | Education             | Numeric | Highest education                                                                                                                                                            | 1=No schooling completed
2=Nursery school to 8th grade
3=Some high school, no diploma
4=High school graduate, diploma or the equivalent (for example: GED)
5=Some college credit, no degree
6=Trade/technical/vocational training
7=Associate degree
8=Bachelor's degree
9=Master's degree
10=Professional degree
11=Doctorate degree |                                                                                                |
| Contact data | intervention-response | Numeric | Did you respond to the social media recruitment message because you would like to learn more about a clinical trial?                                                         | 1=yes 0=no                                                                                                                                                                                                                                                                                                                                                          |                                                                                                |
| Contact data | info_purpose          | Numeric | Are you gathering information for yourself or on behalf of someone else?                                                                                                     | 1=For myself 2=On behalf of someone else                                                                                                                                                                                                                                                                                                                            |                                                                                                |
| Contact data | value                 | Numeric | How helpful would you say is it when research institutions reach out directly to potential clinical trial participants via Twitter?                                          | 1=Very helpful 2=Helpful
3=Somewhat helpful 4=Not helpful at all 5=Don't know                                                                                                                                                                                                                                                                                    |                                                                                                |
| Contact data | concern               | Numeric | How concerned are you about researchers and research institutions monitoring Twitter conversations to identify and contact potential study participants for clinical trials? | 1=Very concerned
2=Somewhat concerned
3=Not too concerned 4=Not concerned at all 5=Don't know                                                                                                                                                                                                                                                                 |                                                                                                |
| Contact data | contact_form_use      | Numeric | Contact used contact form on clinical trial web page                                                                                                                         | 1=yes 0=no                                                                                                                                                                                                                                                                                                                                                          |                                                                                                |
| Contact data | follow-up             | Numeric | USC Norris team followed up with contact                                                                                                                                     | 1=yes 0=no                                                                                                                                                                                                                                                                                                                                                          |                                                                                                |
| Contact data | consultation          | Numeric | Contact had formal consultation with a USC/Norris physician or trial coordinator                                                                                             | 1=yes 0=no                                                                                                                                                                                                                                                                                                                                                          |                                                                                                |
| Contact data | enrolled              | Numeric | Contact enrolled                                                                                                                                                             | 1=yes 0=no                                                                                                                                                                                                                                                                                                                                                          |                                                                                                |
| Message data | day-sent              | Numeric | Day message was sent                                                                                                                                                         | 1=Monday 2=Tuesday
3=Wednesday 4=Thursday
5=Friday 6=Saturday
7=Sunday                                                                                                                                                                                                                                                                                     |                                                                                                |
| Message data | time_sent             | Numeric | Time message was sent                                                                                                                                                        | hh:mm:sec                                                                                                                                                                                                                                                                                                                                                           | Not available for ads since social media networks have an internal process for displaying ads. |

|              |                  |         |                                                              |                |
|--------------|------------------|---------|--------------------------------------------------------------|----------------|
| Message data | image            | Numeric | Image included in the message                                | 0=No 1=Yes     |
| Message data | message_clicks   | Numeric | Total number of message link clicks after 1 week             | 0, 1, 2, 3,... |
| Message data | click_time       | Numeric | Time of click on message link                                |                |
| Message data | impressions      | Numeric | Total number of message impressions after 1 week             | 0, 1, 2, 3,... |
| Message data | retweet_Twitter  | Numeric | Message shares                                               | 0, 1, 2, 3,... |
| Message data | reply_Twitter    | Numeric | Message replies/comments                                     | 0, 1, 2, 3,... |
| Message data | likes_Twitter    | Numeric | Message likes                                                | 0, 1, 2, 3,... |
| Website data | sessions         | Numeric | Website sessions referred to by Twitter message after 1 week | 0, 1, 2, 3,... |
| Website data | clicks           | Numeric | Website link clicks                                          | 0, 1, 2, 3,... |
| Website data | users            | Numeric | Website users                                                | 0, 1, 2, 3,... |
| Website data | exits            | Numeric | Website exits                                                | 0, 1, 2, 3,... |
| Website data | session_duration | Numeric | Duration (in seconds) of users' sessions.                    | 0, 1, 2, 3,... |
| Website data | time_onpage      | Numeric | Time on page                                                 | 0, 1, 2, 3,... |
| Website data | pageviews        | Numeric | Pageviews                                                    | 0, 1, 2, 3,... |

hh:mm:sec  
(Data will be collected using two approaches (1) using third-party application ClickMeter and (B) rails backend (ie, when a webpage is loaded on the educational website itself. The SM platforms and Google don't provide this type of information.)

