| Selection criteria                     | 
Inclusion criteria: Eligible clinical trials must focus on one or more of the pre-selected cancer disease types, i.e., non-small cell lung cancer, prostate cancer, breast cancer, colon cancer, kidney cancer, or lymphoma (trial selection is independent of stage of disease); be a Phase 1 trial in expansion, Phase 2, or 3; be interventional trials; recruit in English; be IRB-approved and open to accrual at USC Norris; recruit for at least 9 months at the point of enrollment; and set monthly accrual target <math>\geq 1</math>/annual accrual target <math>\geq 12</math>.
 
Exclusion criteria: Phase 1 trials in dose escalation.
                                                                                                                                                                                                                                                                                                                                                                                                                                                                                                                               |
| Investigational methods/Intended use   | 
 
1. We will use Sympplr Signals, a healthcare SM analytics platform that maintains a database of curated disease- and health-related Twitter conversations and user data, updated daily and easily sortable by SM user type (patient, physician, health care organization), location and time zone, language, disease/health interests, message content, sentiment, and SM influence. We will use the data to identify users on Twitter in LA County who mention specific disease/health-related keywords and contact them to recruit them into clinical trials. Those individuals are then targeted for recruitment using a combination of SM and traditional methods.
 
2. We will use semi-structured interviews to assess pre-and post-perspectives and concerns among PIs and research team members regarding the use SML and SM recruitment to recruit cancer trial participants.
 
3. We will use brief survey interviews to assess participant satisfaction with recruiting
 
                                                                                                                                                           |

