- Post-qualitative interviews with study team members will be undertaken to explore trial participants' views and experiences of the trial methods and intervention (principal investigators, clinical research coordinators, recruitment specialists). The interview guide is under development and will be submitted to the USC HSCIRB for review. Qualitative research expert [name] (consultant on this project) will advise this part of the study. We will gather a range of data. Please see **Table 3** that lists all outcomes in the *Data analysis* section 3.3.7.

Recruitment of USC Norris clinical trial team members: As we enroll cancer clinical trials in this study, the study co-PI ([name]) will contact the cancer trial PI via email (using USC's email system) to invite the PI and one additional study member (e.g., clinical research coordinator, recruitment specialist) to participate in an interview.

- Brief survey interviews with contacted Twitter users will be conducted by the study teams with prospective study participants who contacted the study team in response to SM recruitment. The goal of the survey is to collect demographic information about the prospective study participants and to better understand their perception of the SM recruitment method used. Qualitative research expert [name] (consultant on this project) will also advise this part of the study. (See **Appendix 6** for the full questionnaire)

Additionally, we will look at the impact of the SM intervention measured by monthly observed recruitment rate vs. monthly projected accrual target. We will calculate the effect size estimate of the number of people to enroll cancer trials as a result of targeted social media listening and recruitment (SML) via Twitter.

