### *3.3.7 Data analysis*

Feasibility will be assessed by describing the acceptance of and satisfaction with the SM recruitment method among USC Norris study team members and Twitter users in LA County, number of cancer trials eligible to be enrolled in study at the time of this study (current estimate of 84 is based on latest data from USC Norris), number of cancer disease types and studies that can be monitored for on Twitter simultaneously by the SC CTSI study team, time and effort it takes the SC CTSI and USC Norris team members to respond to the

resulting inquiries and decide whether or not to bring the patient in for screening, eligibility rate of prospective participants, demographic and ethnic diversity rate of those who consented/enrolled, social media message click rate, website contact form usage rate, social media message click rate, website contact form usage rate. **Table 3** lists all primary outcomes measures we intend to use.

To facilitate qualitative data analysis, we will develop an initial code list based on the interview guide. The code list will be modified throughout the coding process. Each coded transcript will be discussed line by line until the coding team came (Drs. [name] and [name]) to an agreement about code definitions and how they should be applied. Important themes will be summarized and used to understand satisfaction with SM-based recruitment strategies for cancer-related clinical trials.

Count outcomes will be presented as median and interquartile range, nominal outcomes will be presented as N (%). We will explore patient and study characteristics between the two cohorts to examine where differences might lie by including them as potential covariates in the models. Comparisons of the before- and after time periods will be made using generalized estimating equations for appropriate outcome type (Poisson, means, prevalence) accounting for type of cancer.

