| Website contact form usage rate      | Number of times a contact form was used on a trial webpage/Number of webpage sessions ( Sessions: Group of interactions a user takes on a webpage or website within a given time frame, e.g., page views, clicks. )                                                                                                                                                                                                                                                                                     |
| User acceptance and satisfaction (%) | 
 
• Number of USC Norris study team members who are satisfied with the SM monitoring and recruitment intervention/Number of all study team members engaged
 
• Number of PIs that are willing to participate (acceptance by PIs)
 
• Number of trial participants enrolled (Twitter users in LA County) who are satisfied with the SM monitoring and recruitment intervention/Number of all people engaged (i.e., who spoke with the study team)
 
 |
| IMPACT AND EFFICACY           |                                                                                                                                                                                                                                                                                                                                                                                                                                                                                                                |
| Enrolment rate per month             | 
 
• Number of people enrolled per month/Number of people contacted on Twitter per trial per month
 
• Number of people triaged and enrolled in another trial per month/Number of people contacted on Twitter per trial per month
 
                                                                                                                                                                                                                        |

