### 2. Prospective participant data collection sheet

1. Name of prospective participant
  - a. First name
  - b. Last name

2. What's your Twitter handle?
  - a. \_\_\_\_\_
  - b. Prefer not to disclose
3. What's your email?
4. What's your birth date
5. Are you...?
  - Female
  - Male
  - Other
  - Prefer not to disclose
6. How do you describe yourself? (check all that apply)
  - African American / Black
  - American Indian / Alaska Native
  - Asian / Pacific Islander
  - Hispanic
  - Middle Eastern
  - White
  - Other
  - Prefer not to disclose
7. What is the highest degree or level of school you have completed?
  - No schooling completed
  - Nursery school to 8th grade
  - Some high school, no diploma
  - High school graduate, diploma or the equivalent (for example: GED)
  - Some college credit, no degree
  - Trade/technical/vocational training
  - Associate degree
  - Bachelor's degree
  - Master's degree
  - Professional degree
  - Doctorate degree
  - Prefer not to disclose
8. Did you respond to the social media recruitment message because you would like to learn more about a clinical trial?
  - a. Yes
  - b. No
9. Are you gathering information for yourself or on behalf of someone else?
  - a. For myself
  - b. On behalf of someone else

10. How helpful would you say is it when research institutions reach out directly to potential clinical trial participants via Twitter?
  - a. Very helpful
  - b. Helpful
  - c. Somewhat helpful
  - d. Not helpful at all
  - e. Don't know
11. How concerned are you about researchers and research institutions monitoring Twitter conversations to identify and contact potential study participants for clinical trials?
  - a. Very concerned
  - b. Somewhat concerned
  - c. Not too concerned
  - d. Not concerned at all
  - e. Don't know
12. When were you diagnosed with cancer?
13. Do you have active cancer? (Only if yes triage to USC Norris team)
  - a. Is it visible on scans (CT, MRI)?
  - b. Are you on active treatment?
14. Are you able to do activities of daily life independently? (e.g., eating, drinking, bathing)
15. Do you have a copy of your medical records?
16. Are you currently a patient at
  - a. USC Norris Comprehensive Cancer Center, or
  - b. USC Keck Medical Center, or
  - c. LA County USC?
17. Any other comments you want to share (free text)

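### Questionnaire item 10 offers three grades of helpful and one flat negative, so a Twitter-user satisfaction share drawn from it would lean favourable

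*Protocol*

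**What the plan says.** Item 10 of the data collection sheet in Appendix 6 asks: "How helpful would you say is it when research institutions reach out directly to potential clinical trial participants via Twitter". The Appendix 5 data dictionary stores the answer as the variable value. Codes 1 and 2 are Very helpful and Helpful, and the rest are "3=Somewhat helpful 4=Not helpful at all 5=Don't know".

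Item 11, stored as concern, asks how worried the respondent is about researchers monitoring Twitter. Codes 1 and 2 are Very concerned and Somewhat concerned, and the rest are "3=Not too concerned 4=Not concerned at all 5=Don't know".

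The Synopsis gives the purpose of the survey: "We will use brief survey interviews to assess participant satisfaction with recruiting" method. Section 3.3.1 adds that it is meant "to better understand their perception of the SM recruitment method used". Table 3 lists the matching primary feasibility outcome for Twitter users as a ratio: "Number of trial participants enrolled (Twitter users in LA County) who are satisfied with the SM monitoring and recruitment intervention/Number of all people engaged". Section 3.3.7 says that "nominal outcomes will be presented as N" with a percentage. The protocol does not say which answers to item 10 or item 11 make a respondent satisfied.

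**The concern.** Acceptance among Twitter users is half of the first objective (Section 1.3.1) and part of the first primary outcome. Apart from the free-text item 17, items 10 and 11 are the only questions that ask what respondents think of being approached in this way. On item 10, someone who finds the outreach slightly unhelpful has no matching answer. The choice is a weak favourable answer, the strongest negative, or Don't know. Item 11 does offer a mild answer on each side, and the protocol gives no reason for treating the two items differently.

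What is at stake is a feasibility percentage that could look better than opinion warrants. Table 4 says the pilot data will support a larger grant proposal. Respondents are people who chose to get in touch after a recruitment message, so they may already be well disposed, and the response set would push in the same direction.

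**Working it through.** The protocol states no sample size, target or expected percentage for these items, so there is no figure to reproduce. The check is a count of options, followed by illustrations on assumed answer distributions.

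**1. Count of substantive options (Appendices 5 and 6)**

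| Item | Favourable | Unfavourable | Mild negative offered? |
|---|---|---|---|
| 10, value | 3 (codes 1, 2, 3) | 1 (code 4) | No |
| 11, concern | 2 (codes 3, 4) | 2 (codes 1, 2) | Yes (code 2) |

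**2. From item to outcome.** Table 3 needs a proportion, so answers must be divided into satisfied and not satisfied. No item asks about satisfaction directly. The literal division of item 10 is codes 1 to 3 against code 4.

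**3. Even spread over the four substantive answers (assumed)**

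- Item 10 as written: 3/4 = 75% favourable.
- Balanced set of two and two: 2/4 = 50%.
- Difference: 25 percentage points.

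**4. Same spread with a share d of Don't know kept in the denominator (assumed)**

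Favourable share = 0.75 × (1 − d) as written, and 0.50 × (1 − d) if balanced.

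| d | As written | Balanced | Difference (points) |
|---|---|---|---|
| 5% | 71.25% | 47.5% | 23.75 |
| 10% | 67.5% | 45.0% | 22.5 |
| 20% | 60.0% | 40.0% | 20.0 |
| 30% | 52.5% | 35.0% | 17.5 |

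Within the first results column, the percentage falls by almost 19 points (71.25 − 52.5 = 18.75) solely because of how many people answer Don't know. The handling of that answer therefore has to be visible in the report even when only percentages are shown.

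**5. Dependence on the cut-off.** If a share s of respondents choose Somewhat helpful, counting codes 1 to 3 instead of codes 1 and 2 raises the favourable percentage by exactly s. For assumed s of 10%, 20%, 30% and 40%, the gap is 10, 20, 30 and 40 points.

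Steps 3 to 5 show direction and sensitivity. None of them estimates what this survey would find.

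**The case against.** Helpfulness can reasonably be graded from none to very, and an even split of options is not a rule. Reported category by category, Somewhat helpful is visible as the weak answer it is. A lean arises only if all three helpful answers are pooled, and the protocol sets no such cut-off. Nor does it label value and concern as the satisfaction measure. An uneasy respondent can choose Don't know or write a comment under item 17. The 75% against 50% comparison assumes that people choose at random among the options.

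Much of this stands. The link from item 10 to Table 3 is an inference from the survey's stated purpose, and the option count is not an effect estimate. What remains is that Table 3 asks for a proportion, so some division has to be made, and item 10 is one of only two closed items that could supply it. Full reporting by category still cannot show a mild negative that nobody was able to choose.

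A reader might also infer, from the Numeric type and code 5, that Don't know will be analysed as the far end of a scale and will distort a mean or Cohen's D. The documents do not support that. Numeric is the dictionary's storage type for coded categories generally: gender is Numeric with "1=Male 2=Female", and day of the week is stored in the same way. Section 3.3.7 reports nominal outcomes as counts and percentages. Its models, including those for means, are for before/after comparisons, and Cohen's D appears in the efficacy paragraph on group differences. Items 10 and 11 are put only to people who responded to the outreach, so they have neither a before period nor a comparison group.

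**Conclusion.** The point holds as a modest fault in the instrument. Item 10 is unbalanced three to one, its companion item 11 is balanced, and a helpful/not-helpful split of item 10 would lean favourable in a primary feasibility outcome. The size cannot be computed from the documents. The 25 points (75% against 50%) are a count of options under an assumed even spread.

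The conclusion rests on two assumptions: that item 10 contributes to the Twitter-user satisfaction proportion, and that the helpful answers are pooled. A reader might go further and say that the acceptance result is biased. That is not shown, because the protocol does not fix how answers become satisfied or not. The reason to act now is that the wording cannot be corrected once answers have been collected, whereas the cut-off and the handling of Don't know still can be.

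**What to change.** Before the first interview:

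- **Item 10 in Appendix 6 and value in Appendix 5:** change the substantive options to Very helpful / Somewhat helpful / Not very helpful / Not helpful at all, mirroring the form of item 11.
- **Favourable answers, fixed in advance:** codes 1 and 2 on value, and codes 3 and 4 (Not too concerned, Not concerned at all) on concern. The two items run in opposite directions, so a rule taking the first two codes on both would count worried respondents as accepting.
- **Don't know:** report it as its own percentage on both items.

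The cost is a small wording change to the questionnaire and data dictionary, with notice to the IRB. It needs no extra data and no extra respondents.
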